### Interventions

Both experimental conditions consist in 2*45 min of group interventions per week over 6 months (~ 40 sessions in total) in small groups (n ~ 3–4) plus short daily exercises to perform at home (~ 30 min/day, 4* per week). The passive control group will not receive any intervention and only take part in the measurements.

### Experimental condition / Intervention 1: musical practice group intervention

The musical practice group will receive interventions with steel "tongue drums", provided by a therapist (a professional musician at MSc level) who has experience working with elderly and patients in groups. Different styles of music are played ("from Bach to the Beatles"). Steel tongue drums are modern percussion instruments of the idiophone family, relatively small (the ones we use are 12 inches / 30.5 cm) and thus easily manageable. They are delivered with a small bag for transportation, and each participant will receive an instrument to take home for the duration of the intervention. The instruments we chose dispose of 13 half-tones or minor seconds, thus composing together a full chromatic octave plus one note (an octave above the lowest note). These instruments can be played with the hands and fingers or with drumsticks. Their advantages are that they provide strong sensorimotor feedback, and that their tonal range allows producing melodies and harmonies together. Then, they generate a pleasant mellow sound. They are low cost and very suitable for group play. During the interventions, individual and group instruction, also with accompaniment by the teacher, are alternated. The therapist assigns homework encompassing musical exercises and rehearsal of musical pieces learned during the lessons to be performed daily (~ 30 min/day). A simple form of music notation using numbers and recordings will assist the patients during homework. Classical music notation may be used after t1, according to group level.

### Experimental condition / Intervention 2: psychomotor treatment group intervention

Based on a holistic vision of the human being, the psychomotor approach targets the interdependence between sensorimotor, cognitive, and emotional development. This body-mind training focuses on movement, particularly on developing the body schema. It proposes activities like Tai Chi, involving slow controlled movements, but is more inward-oriented. Psychomotor treatment involves interactions between physical, emotional and cognitive processes, aiming to enhance body-awareness.

Body exploration through conscious auto massage, tonic regulation exercises, balance, posture, and movement exercises are performed either with open or closed eyes. Emotion mime and recognition are part of the interventions. The incorporation of the entire body in game or drama settings, as well as postural imitation exercises, round out this training regimen. The sensory and emotional sensations following the exercises are discussed with the patients to enhance cognitive representation. This approach is used in various pathological contexts. A certified psychometrician, experienced in working with cognitively impaired elderly, will provide the interventions. Workouts performed during the interventions and simple exercises explained during the training should be performed at home daily (~ 30 min/day).

### Passive control condition

In this longitudinal study, the healthy participant group serves as a control for age-related natural brain atrophy and test–retest effects at the psychometric battery and fMRI tasks.

There is an additional reason for adopting a healthy control group: one of the university hospital memory clinics where we recruit our patients does not accept active or passive control groups of patients in non-drug intervention studies, because they provide no benefit to the patients. The healthy passive control group participants must adhere to the same inclusion and exclusion criteria as the experimental groups, except for an MCI diagnosis. They will be assessed in the same way as the experimental groups (battery and MRI measurements at t0, t1 and t2). Control participants will be matched to the experimental groups for age, gender and education level.

### Setting

For Geneva participants, music interventions and passage of the behavioral test battery take place at the Geneva School of Health Sciences (Haute Ecole de santé de Genève (HEdS-GE) of the University of Applied Sciences and Arts Western Switzerland (HES-SO)). The psychomotor training takes place at the Department of Psychomotricity (Haute école de travail social de Genève, HETS-GE) of the University of Applied Sciences and Arts Western Switzerland HES-SO, Geneva School of Social work. Brain imaging (MRI) is performed at the BBL, the Brain and Behaviour Laboratory at the University Medical Center of the Geneva University.

For Lausanne participants, all interventions and passage of the behavioral test battery take place at the Leenaards Memory Center of the CHUV, and brain imaging (MRI) will be performed at the Laboratoire de recherche en neuroimagerie (LREN; Laboratory for Research in Neuroimaging) in the same building, also at the CHUV.

### Study population

#### Inclusion and exclusion criteria

### Inclusion criteria

1. MCI diagnosis by experts at the memory clinics; 2. MMSE score (Mini-Mental State Examination) [64] ≥ 23 or MoCA ≥ 17 [130, 131]; 3. Hospital Anxiety and Depression Scale (HADS) [127] < 14 (< 7/21 for anxiety and < 7/21 for depression); 4. Age between 60 and 80 years; 5. Right-handedness [132]; 6. Fluent in French; 7. Able to give informed consent as documented by signature.

Only right-handed participants will be included, because a minority of left-handed individuals show a different hemispheric organization, e.g. for language and music functions [133–135]. Left-handed participants could induce variability in the data and diminish experimental effects. Right-handed persons represent more than 90% of the population.

### Exclusion criteria

1. Serious motor deficits; 2. Impaired/not-corrected hearing 3. Serious physical and mental comorbidities; 4. Participation in physical or cognitive training over the last 12 months; 5. Maximum 5 years of official music education over the lifespan outside the school curriculum or during the last 3 years; 6. Intensive physical activity over the last 12 months (sports or body-mind exercises); 7. Left-handed or ambidextrous; 8. MRI incompatibility (claustrophobia, cardiac stimulator, implants…).

### Recruitment, prescreening and informed consent procedures (experimental groups)

The recruitment takes place at the Memory Center of the HUG (MC-HUG) in Geneva, and at the Leenaards Memory Center of the CHUV (LMC-CHUV) in Lausanne. Diagnosis of MCI is performed by specialized neurologists of the MC-HUG and the LMC-CHUV. At each site, a collaborator will call the patients who correspond to the profile and ask if they would like to engage in a 6-month intervention that includes either musical or physical training twice a week, as well as brain and behavior measures that will be repeated 3 times. The patients who manifest an interest in participating in the study will receive a letter to confirm the information exchange with the MC-HUG or the LMC-CHUV. They will be contacted by phone several days later by the clinical psychologist of the research team to perform a more thorough check concerning the inclusion/exclusion criteria and to provide more extensive information on the interventions and the randomization procedure.

If the patient seems compatible with the criteria and interested in participating, the declaration of informed consent, a summary information sheet and a series of questionnaires (demographic, cognitive reserve index, daily living activities, musical activities, physical activities & stressful life events; for details and references, see the section Measurements and Procedures and Supplementary Table 1) will be sent to their home address to fill in alone or with a caregiver. After reading the information sheet, before filling in any questionnaire, the patient/participant should sign the declaration of informed consent. During the first laboratory visit, the clinical psychologist of the research team will first countersign the declaration of informed consent and then check and finish completing the questionnaires, together with the patient, at the HEdS-GE or LMC-CHUV (see Supplementary Table 1**)**. By doing so, the psychologist verifies in detail whether all inclusion and exclusion criteria are met.

During the first lab visit (see Supplementary Table 1, Prescreening step 3), each potential participating patient will be asked to bring their signed informed consent that will be countersigned in his/her presence by the clinical psychologist. The participating patient will then receive more precise oral and written information on the study procedure. The documentation is adapted to the patient population to facilitate understanding. The information will cover the prescreening (inclusion/exclusion criteria) and its rationale, the randomization into 2 intervention groups, the pre (t0), intermediate (t1) and post-intervention (t2) behavioral testing (psychometric battery) and MRI recordings, and their potential inconveniences (fatigue, noise, etc.). If the patient still agrees to participate, and all information is clear, and if they meet all the inclusion/exclusion criteria, the informed consent can be considered validated. If not so, the informed consent form and all information on the patient will be destroyed.

A copy of the signed informed consent will be given to the participating patients.

### Consent (all groups, control group included)

Consent to voluntarily participate in the study implies: the right to withdraw at any time, consent to the use of the collected data for scientific and educational purposes (provided that the data remain anonymous) and finally, to inform the participants directly or their treating physician, in case of unexpected potential detection of abnormalities.

### Documents and information provided to the participants

In chronological order the patients/participants will receive the declaration of informed consent, a summary information sheet, extensive oral information during the first lab visit, a trust agreement^5^ to sign, a MRI safety questionnaire to be filled in before each MRI measurement, a homework questionnaire (weekly report on estimated time spent on homework), and an authorization for use of image (on a voluntary basis), as we will in principle film the interventions once per month in order to perform qualitative analyses on the learning process.

### Compensation for the MCI patients (experimental groups)

The compensation for the MCI patients consists in 6 months of free interventions, and reimbursement of transportation costs with the Geneva or Lausanne public transport system (insofar as possible).

### Recruitment, practical details

The recruitment should have started for the first wave of patients in May 2020. Finally, the COVID-19 epidemic caused a 4–5 months delay in the original schedule, and we started recruitment in September 2020 lasting till November 2020.

Mainly because of the anxiogenic and restrictive context of COVID-19, but also for personal reasons (too much time involved, etc.), most patients that seemed to fulfil the criteria initially contacted by the MC-HUG finally chose not to participate. In the end, only 14 patients that met all criteria consented to participate, and of those 4 more interrupted their participation, 2 who went into early dementia, one quit for health reasons and a last individual for personal reasons. Ten patients followed the interventions and passed the measurements, which is not enough for valid analyses (see the section Statistical power of the study).

Therefore, we recruited a second wave of patients at the LMC-CHUV, participating in the study from November 2021 to July 2022 (prescreening, interventions, and all measurements), and a third wave participating between July 2022 and April 2023. We intend to recruit enough patients to bring the total to 16 for both experimental groups. Baseline measures (t0) for the second wave started in December 2021, and for the third wave from August 2022, after the inclusion process (pre-screening and first visit).

### Recruitment and procedure for the passive control group

Healthy passive controls will be recruited in the Geneva area among community-dwelling elderly from February 2022, through advertisements in local (elderly) journals, elderly centers (flyers, posters), and on the internet (i.a. www.planetesante.ch), once the recruitment of the experimental groups is over, to allow matching with the experimental groups.

Participants will be informed about the study's aims and the role of a control group and must, in principle, consent to pass all 3 measurement points (t0, t1, t2). Except for the MCI diagnosis, the same inclusion/exclusion criteria apply to this group as to the experimental groups. They will receive financial compensation by means of gift vouchers. We will first recruit a larger pool than necessary, to allow matching to the patient group.

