### Design, interventions and setting

### Study design

The proposed study is a 1) block-randomized, 2) 3-arm, 3) multicentric (HUG^3^, Genève; CHUV^4^, Lausanne), 4) national (Switzerland), 5) intervention study.

Blocked randomization is applied to the experimental groups only, blocking for the factors 1) age, 2) gender, 3) COGTEL weighted score [80] and 4) MCI diagnosis (1. amnestic; 2. non-amnestic) to balance both intervention groups for those factors. Experts at the memory clinics will select MCI diagnosed patients for participation.

We use a three-arm design: 2 experimental groups of MCI patients, and one matched passive healthy control group. Except at the level of statistical analyses, no blinding is applied.

The blocked (or stratified) randomization procedure is performed at each site separately, aiming to achieve an equal number of music and psychomotor groups at each site, using Ward’s Hierarchical Agglomerative Clustering Method [126]. We will use this method to establish duplets that are maximally similar with respect to the 4 blocking factors, based on minimum Euclidean distance. Subsequently, an algorithm will attribute randomly one participant of each duplet to each experimental group. So, half of the participants will end up in the music practice intervention (n ~ 16), and the other half in the psychomotor intervention (n ~ 16). A control group of matched (age, gender, education level) healthy controls (n ~ 16) that are not part of the randomization process, will be recruited in Geneva, and will receive financial compensation (gift vouchers).

In the documentation that we will provide to the patients we mention that there are 2 different intervention groups that we want to compare for their effectiveness to improve cognitive and motor function, and that for scientific reasons the repartition to the groups will be determined by chance. We will also mention that if patients refuse to accept their group allocation, they cannot participate in the study.

The psychometric battery consists exclusively of validated tests. Cognitive screening at the HUG and the CHUV is similar. The HUG uses the MMSE score [64] and the Hospital Anxiety and Depression Scale (HADS) [127]. At the CHUV the test used for general cognition is the Montreal Cognitive Assessment (MoCA) [128, 129]; they also use the HADS.

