### Duration of the study for each patient

For the experimental groups, the pre-screening period and baseline (t0) testing will take place within approximately 6 weeks before the onset of the interventions. Both intervention groups will receive ~ 40 interventions of 45 min, 2 per week, divided over 6 months. Mid-intervention testing will take place approximately after 3 months of intervention and the post-intervention testing within a maximum of 4 weeks after the last intervention.

The total duration for an average patient to participate in the study therefore takes approximately 9 months, within a period stretching from November 2020 till July 2021 for the first wave of patients and from November 2021 till July 2022 for the second wave. For the third wave the period will extend from July 2022 to April 2023.

For the control group prescreening and baseline measurements will start in March–April 2022, the t1 measurements will take place in June-July, and the t2 measurements in September–October 2022.

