### Before (t0, baseline), after 3 months (t1) and 6 months (t2) of interventions

#### A. Psychometric battery. Total duration: ~75 min. (interrupted by breaks)

D2-R test [88, 89]. Assesses attention, visual scanning accuracy and speed—8 min.Trail making Test A & B [90]. Visuo-motor task, assesses selective visual attention, processing speed and mental flexibility (Shifting)—5 min.Go-No-Go [91]. Inhibition task—5 min.Purdue Pegboard [94]. Evaluates visuo-manual skills and bimanual coordination—10 min.The Clock Drawing test [93] Evaluates apraxia and fine motor control and cognitive functions (visuo-construction, memory, spatial perception/representation, executive functions)—5 min.Laterality recognition test [96]. Assesses right/left judgements of body parts presented by photos on a tablet), evaluates the representation of the body schema- 10 min.Unipedal balance test [95] – < 5 min. Evaluates whole body balance.ERQ: Emotion Regulation Questionnaire [121]—10 min.WHOQOL-BREF [98]—5 min. Assesses well-beingCOGTEL [79, 80]. Provides a main (weighted) score of core cognitive function -10 min.

Nota bene: We will measure the COGTEL first during the prescreening (Supplementary Table 1, PRE-SCREENING STEP 3), then at t1 (3 months) and t2 (6 months) within the psychometric battery.

The Amsterdam Instrumental Activity of the Daily Living Questionnaire (Short Version; (A-IADL-Q(SV)) [97] – 25 min will be first filled in at prescreening, then sent by post at t1 and t2 (filled in with the caregiver, then verified in the laboratory).

A detailed list of the different psychometric measurements is provided in Supplementary Table 2.

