#### B. (f)MRI measurements; Total duration ~ 45 min + 15–30 min. of installation/preparation

Grey matter volume assessment [139] (MP2RAGE (Magnetization-Prepared 2 Rapid Acquisition Gradient Echoes)—8 min.White matter assessment, allowing to compute i.a. Fractional Anisotropy (FA) for evaluating white matter integrity reflecting structural connectivity [140] (Diffusion Tensor Imaging, DTI)—7 min.Resting-state functional MRI, allows to measure activity in the Default Mode Network (DMN) reflecting global functional connectivity of the brain [141]; (Echo-planar imaging, EPI)—10 min.Task-related brain activity (task-fMRI). Letter n-back visual working memory task (2- (EPI)—15–20 min. (see fMRI n-back visual working memory task below).

The MRI measurements do not require any special preparation (such as having to drink or be injected with contrast materials or radioactive dye). Acquisitions are performed on a 3 T (Tesla) whole body Siemens Trio system (Siemens TIM-TRIO, Erlangen, Germany) in Geneva and on a 3 T whole body Siemens Prisma scanner (Siemens Prisma, Erlangen, Germany) in Lausanne.

We adapted the default sequences' parameters, opting for a compromise between a good signal-to-noise ratio and a minimum amount of time. The Siemens MRI protocols are optimally synchronized between the TRIO and PRISMA scanners at both sites. For the functional acquisitions, we adopted a multiband echo planar imaging fMRI with an accelerator factor of 3, allowing to reduce the repetition time to 1.350 s, which represents a good temporal resolution for fMRI (see Supplementary Table 3). Following these choices, we could reduce the total duration of the MRI scanning to 45 min, which is important in the context of our MCI patient population.

A detailed list of the different MRI measurements (*n* = 4) and main protocol parameters are provided in Supplementary Table 3.

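### On the stated dates, controls are recruited and baselined before wave 3 is enrolled, so they can be matched only to waves 1 and 2; they also come from one site

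*Protocol article*

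**What the plan says.** Three sections of the protocol article fix the calendar.

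- *Recruitment and procedure for the passive control group*: "Healthy passive controls will be recruited in the Geneva area among community-dwelling elderly from February 2022", and this happens "once the recruitment of the experimental groups is over, to allow matching with the experimental groups". A pool larger than needed is recruited first so that matching is possible. Its size and the moment of selection are not given.
- *Recruitment, practical details*: wave 1 was approached through the Geneva memory clinic and left 10 patients who completed. Wave 2 was recruited at the Lausanne clinic, with baseline from December 2021. There is then "a third wave participating between July 2022 and April 2023", with baseline from August 2022 once its inclusion is done. The site of wave 3 is not stated.
- *Duration of the study for each patient*: controls begin prescreening and t0 in March or April of 2022. For their later visits the section says that "the t1 measurements will take place in June-July, and the t2 measurements in September–October 2022".

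On place, *Study design* describes controls "that are not part of the randomization process, will be recruited in Geneva". *Setting* sends Geneva participants to the Geneva imaging facility and Lausanne participants to the Lausanne one. The MRI section gives a Siemens Trio in Geneva and scanning "on a 3 T whole body Siemens Prisma scanner (Siemens Prisma, Erlangen, Germany) in Lausanne". Matching is on age, gender and education level.

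On timing of the primary outcome, the battery section notes: "We will measure the COGTEL first during the prescreening". Prescreening and baseline fall within about 6 weeks before training, and the final test within 4 weeks after the last session.

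**The concern.** The primary outcome and its analysis are defined as change in the COGTEL weighted score in each patient group against the passive control group. The controls' stated job is to account for natural brain atrophy and for test–retest effects. They are not randomized, so the credibility of that comparison rests on matching and on similar measurement conditions. The matching rule presupposes that the patients are known when controls are chosen. If a whole wave enters later, a group reported as matched to the patients will have been chosen without sight of part of them.

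Two further differences bear on the same contrast. Controls share a site, and by inference a scanner, with only some of the patients. The patients' COGTEL retest interval also has slack at both ends that may not be the same in controls.

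**Working it through.** **Calendar, from the article's own dates**

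| Event | Controls | Wave 3 |
|---|---|---|
| Recruitment or participation starts | February 2022 | July 2022 |
| Baseline (t0) | starts March–April 2022 | from August 2022 |
| 3-month visit (t1) | June–July 2022 | after August 2022 |
| Final visit (t2) or end of participation | September–October 2022 | April 2023 |

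- Control recruitment to start of wave 3: February to July = 5 months.
- Control baseline to wave-3 baseline: April to August = 4 months; March to August = 5 months.
- End of control t2 to end of wave 3: October 2022 to April 2023 = 6 months.

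On this schedule controls have had t0 and t1 before any wave-3 baseline. In July 2022, when wave 3 begins, they are at mid-study. The February 2022 start does fit waves 1 and 2, since wave-2 baseline began in December 2021.

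**How much of the sample is affected.** The size of wave 3 is not given. With 10 wave-1 completers, waves 2 and 3 together must supply 32 − 10 = 22 patients to reach the target, or 24 − 10 = 14 to reach the stated minimum of 12 per group. The split between the two waves is not stated, so the wave-3 share cannot be computed.

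**Site.** No control is from Lausanne. If wave 3 is also in Lausanne (an assumption), the Lausanne share of patients is 22/32 = 69% at target or 14/24 = 58% at the minimum. If wave 3 is in Geneva, the share is wave 2 alone, of unknown size.

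A scanner offset that is constant over time cancels in within-person change. What remains is a site-by-time difference δ. With a share p of patients in Lausanne and none of the controls, an unadjusted patient-versus-control change contrast shifts by p × δ. The documents give no δ. For an assumed 0.1 to 0.5 SD and the shares above, the shift runs from 0.583 × 0.1 = 0.06 SD to 0.688 × 0.5 = 0.34 SD.

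**Retest interval.** For patients, COGTEL is first taken at prescreening, up to about 6 weeks before training, and last taken up to 4 weeks after it. For controls the nominal span is March–April to September–October, or 6 months. The patient interval may therefore be somewhat longer, but these windows are limits, not averages, and they do not fix the difference.

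**The case against.** Several points on the other side stand.

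- *Matching is not ruled out altogether.* A reader might infer that it cannot be done at all. The article describes matching to groups, not pairs, and waves 1 and 2 were known or under way by February 2022. If the whole pool were measured and selection left until wave 3 is enrolled, group-level matching to the final sample would be possible. The article does not say that this is planned. Its closing remark that dates may change does not remove the conflict between the sequence and the dates it gives.
- *A count of patients without a matched control* is tempting but has no meaning here. With about 16 controls for 32 patients, at least half would lack an individual match under any schedule.
- *Full confounding with site* might also be inferred. Wave 1 came through Geneva, so site and patient status are only partly aliased. The scanner sequences were synchronized, and baseline scores enter the models. COGTEL uses no scanner. Scanning of controls on the Trio is itself inferred from the *Setting* section.
- *A large fixed gap in retest interval* is not shown. Adding every patient maximum and setting the sum against the controls' nominal interval compares unlike quantities. On their own windows, controls could run from early March to late October, about 35 weeks. They too have a prescreening and are to be assessed in the same way as patients.
- *The randomized comparison is untouched*, because allocation to music or psychomotor training is done within site.

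Some of the site argument survives. Wave 1 is only 10 completers over two arms, measured between November 2020 and July 2021, whereas controls are measured in 2022. Site can be modelled, but on thin data and partly entangled with calendar period.

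**Conclusion.** The point holds in a limited form. The stated order of recruitment contradicts the stated dates, and on those dates the matching rule cannot be followed for wave 3. As scheduled, the controls are matched at best to waves 1 and 2. This weakens the non-randomized contrast that defines the primary outcome, by an amount that depends on the unstated size and make-up of wave 3.

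Single-site controls are a secondary weakness. It is confined to site-by-time effects on MRI change; any figure for it rests on an assumed site for wave 3 and an assumed δ. The retest interval is a minor one, possibly somewhat longer in patients by an amount the article does not determine. Neither supports a claim that patient-versus-control differences are uninterpretable, and the music-versus-psychomotor comparison is unaffected.

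**What to change.** 1. Reconcile the two recruitment sections and the duration section so that sequence and dates agree. State the site of wave 3 and when controls are selected from the pool.
2. Choose one of two routes. (a) Baseline part of the over-recruited pool alongside wave 3, or measure the pool and make the final selection after wave-3 enrolment. (b) Stop describing controls as matched to the full patient sample, and prespecify adjustment of patient-versus-control contrasts for age, gender and education. These variables are already collected, and the mixed models already allow demographic terms.
3. In the mixed model for COGTEL, use actual elapsed time since each person's COGTEL baseline in place of nominal visit months.
4. In patient-versus-control MRI contrasts, include site-by-time, or give a Geneva-only sensitivity analysis.

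The cost is corrected wording, a few lines of prespecification and, under route (a), rescheduling some controls or measuring more of them. Control contrasts become slightly less precise, and a Geneva-only analysis would be small.

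### The control recruitment dates do not allow the promised matching to the final patient groups, because a third patient wave enters after the controls' baseline

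*Protocol article*

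**What the plan says.** Under Passive control condition the article promises: "Control participants will be matched to the experimental groups for age, gender and education level". Study design names the same three variables and places the controls outside the randomisation.

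The section on recruitment of the passive control group states a starting date, "Healthy passive controls will be recruited in the Geneva area among community-dwelling elderly from February 2022". The same sentence adds an ordering rule with its reason: "once the recruitment of the experimental groups is over, to allow matching with the experimental groups". That section also plans a pool larger than needed so that matching is possible. It gives neither the size of the pool nor the time at which the final controls are picked.

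Duration of the study for each patient sets the control calendar. "For the control group prescreening and baseline measurements will start in March–April 2022", t1 follows in June–July, and "the t2 measurements in September–October 2022".

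The patient calendar is in that section and in Recruitment, practical details. Wave 1 is finished with ten completers. Wave 2 began baseline in December 2021. Then comes "and a third wave participating between July 2022 and April 2023", with baseline from August 2022 once its inclusion process is done. The text still describes reaching 16 per experimental group as an intention.

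**The concern.** The ordering rule exists so that the composition of the patient groups is known when controls are chosen. On the stated dates it is known for waves 1 and 2 only.

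This matters because the primary outcome sets each patient group against the controls, a contrast that randomisation does not protect. The controls are there to represent retest gain and natural atrophy over six months. Age and education can plausibly affect both. If the control set is fixed before wave 3 is seen, the statement that controls are matched to the experimental groups claims more than the schedule can deliver.

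**Working it through.** **Step 1. The dates side by side.**

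| Event | Controls | Patient wave 3 |
|---|---|---|
| Recruitment or entry | from February 2022 | from July 2022 |
| t0 | March–April 2022 | from August 2022 |
| t1 | June–July 2022 | not dated separately |
| t2 or end | September–October 2022 | April 2023 |

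Control recruitment starts 5 months before wave 3 enters. Control t0 precedes wave 3 t0 by 4 to 5 months, and control t1 is over before any wave 3 baseline. Control t2 ends 6 to 7 months before wave 3 does. The ordering rule would fit a two-wave trial, since wave 2 was already at baseline in December 2021. It does not fit three waves. That the sentence was simply not updated when wave 3 was added is a plausible inference, not something the article says.

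**Step 2. How large could the imbalance be?** The article gives no figure to reproduce, and it does not state how the patients divide between waves 2 and 3. Let k be the number of wave 3 patients among 32. Assume that controls match waves 1–2 perfectly and that waves differ only by chance. In units of the covariate's SD:

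- gap = (k/32) × (mean of wave 3 − mean of waves 1–2)
- SD of gap = (k/32) × √(1/k + 1/(32 − k))

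The central value k = 11 comes from (32 − 10)/2, an assumed even split of the patients still needed after the ten wave 1 completers. The range 6 to 16 is also assumed.

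| k | Share of 32 | SD of gap | Chance that the gap exceeds 0.2 SD either way |
|---|---|---|---|
| 6 | 19% | 0.085 | 2% |
| 11 | 34% | 0.128 | 12% |
| 16 | 50% | 0.177 | 26% |

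Reference with no matching, 16 controls against 32 patients: √(1/16 + 1/32) = 0.31.

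The primary comparison takes each arm separately. For one arm of 16 with k = 5.5, the SD is (5.5/16) × √(1/5.5 + 1/10.5) = 0.18. The unmatched reference is then √(1/16 + 1/16) = 0.35.

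**Step 3. From covariate to outcome.** A covariate gap reaches the outcome only after multiplication by the covariate's association with change. For an assumed correlation of 0.1 to 0.5, a gap of 0.13 SD becomes 0.13 × 0.1 = 0.013 to 0.13 × 0.5 = 0.065 SD of change. The power section plans on f = 0.65, which for two groups is d = 2 × 0.65 = 1.3.

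**The case against.** The best defence is the larger pool. If every member of it were tested at t0, t1 and t2, a matched set could be drawn after wave 3 is in. A reader might infer from the dates that matching is impossible, and the documents do not support that. Nor do they support the opposite: they never say that surplus controls are tested or that selection is deferred, and they keep a target of 16 controls. The general caveat in the Discussion that dates may change shows the calendar is provisional, but it does not reconcile statements that conflict as written.

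A reader might also infer that matching is the only safeguard and that any mismatch passes straight into the treatment comparison. Neither holds. Baseline scores enter the models, and the eligibility criteria are shared apart from the diagnosis. The article also notes that mixed models can take demographic data. Baseline adjustment deals with starting level rather than with age or education as such, so part of the concern stands. The absence of a fixed covariate list is not itself a fault, because a protocol article commonly leaves it to the analysis plan.

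Finally, one might suppose that wave 3 differs systematically from the earlier waves. Wave 1 came from the Geneva clinic and wave 2 from Lausanne, so interchangeable waves are an assumption. The article gives no basis for putting a size on any such shift.

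**Conclusion.** The inconsistency is real: the ordering rule for controls cannot be kept on the stated dates. Prospective matching to the final groups is therefore not delivered unless an unstated later selection from a fully tested pool is intended.

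The size is modest. Under the assumed wave 3 share of 6 to 16 of 32, the chance gap has an SD of about 0.08 to 0.18 covariate SD, so much of the benefit of matching survives. These figures rest on the assumed split, perfect matching to waves 1–2 and interchangeable waves. Subtracting completers from a recruitment target is a rough way to reach the central value, since 14 wave 1 patients consented.

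The randomised comparison of music with psychomotor training is not affected. The deliberate difference between healthy controls and patients is a separate matter.

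**What to change.** Reconcile the sections on patient recruitment, control recruitment and study duration by one of two routes:

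- **(a)** State that the larger pool is tested at t0, t1 and t2, and that the matched controls are selected after wave 3 inclusion closes by someone blind to outcomes. The cost is testing and scanning the surplus controls; their number is not given.
- **(b)** State that controls are matched to waves 1–2 only. The cost is a change of text.

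In either case, put age, gender and education level into the patient-versus-control mixed models as covariates, and report standardised differences on them for the patients actually analysed. The demographic questionnaire already collects all three, so this costs a sentence in the analysis plan.

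Holding back some control places until wave 3 inclusion closes is optional. It adds no participants, but control testing and MRI would run to about April 2023 instead of October 2022, and the number to hold back depends on a wave split that the article does not give.
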